## **5.0 METHODS: MONITORING**

### **5.1 Data monitoring**

An independent Data Safety Monitoring Board (DSMB), consisting of 2 experts in clinical research in intensive care and 1 bio-statistic will be established before patient enrolment. The DSMB Charter will be prepared by the steering committee and signed by the members of the DSMB before the trial commences. The DSMB will have access to all results and make the appropriate considerations about the appropriateness of the sample size, the efficiency and quality of data collection system, eventual occurrence of suspected protocol-related adverse event. The DSMB has the right to stop the trial for safety reasons.

#### Analyses ad interim

Considering a statistical approach based on two phases, an interim analysis is planned after the randomization of 90 patients (50% of sample size) for the double objective of monitoring safety and verifying the accuracy of the assumptions made for sample size estimation regarding the primary end-point event rate in relation to the anticipated survival benefit. With the interim analysis we will be able to evaluate whether there is a substantial superiority of one treatment. The obtained results will be evaluated by the DSMB and by the steering committee and, in case of significant differences in survival among the groups, all patients will be switched to the most promising treatment.

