### **3.0 METHODS: ASSIGNEMENT OF INTERVENTIONS**

#### **3.1 Allocation and blinding**

A block randomisation will be used with variable block sizes (block size 4-6-8), stratified by 3 factors: Centre, BMI (<30; ≥30) and Age (<75 e ≥75). Central randomisation will be performed using a secure, web-based, randomisation system. The allocation sequence will be generated by the study statistician using computer generated random numbers. The attending physician, according to the protocol and the randomization, will note the inclusion of the patient in the study. Clinicians will receive all the instructions to attend the protocol and paper printed instructions will be distributed in the participating centres. The local coordinator will be responsible of the training and information of the personnel about the study protocol. The study is conceived as open-label: the patients and all the healthcare personnel will be aware of the group allocation.

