### **5.2 Harms**

All the patients, regardless the inclusion in the study and the randomization group, will benefit from the best standard of care following the principles of Good Clinical Practice. Intensive care patients frequently develop life-threatening organ failure unrelated to study interventions and despite optimal management. Therefore, events that are part of the natural history of the primary disease process or expected complications of critical illness  will not be reported as adverse events (AE) in this study. All the included patients will be intensively monitored following the standard procedures of the Intensive Care and any suspected protocol-related AEs will be reported. The steering committee (SC) and the DSMB will evaluate the adverse events occurred during the study. For every AE, the SC and the DSMB must assess the intensity (severity) and causality (relationship to study treatment). Specifically, the intensity of events should be classified as mild, moderate, or severe. The assessment of causality will be based upon the categories of related and not related. These classifications should be based on the following definitions:

The intensity (severity) of a specific event is defined as follow:

Mild: AE which is easily tolerated;

Moderate: AE sufficiently discomforting to interfere with daily activity;

Severe: AE which prevents normal daily activities.

Causality assessment is required for all clinical investigation cases. The relationship between an AE and a product is considered:

Possibly related: if, after careful assessment, a possible connection with the use of the investigational product cannot be ruled out;

Not-related: if the AE is due to causes not related to the investigational product.

Events considered “Possible” related to the study treatment, if considered unexpected, will be reported to appropriate regulatory authorities.

All AEs which occur during the course of the study should be recorded within 24 hours in the eCRF. Information on the AE must be recorded on a specific AE form (included in the Investigator’s Site File) and forwarded to the DSMB and to the safety board. Moreover, the eCRF will ensure that an automatic email will be generated and sent directly to the Principal Investigator accountable to receive the study safety information. Each Investigator will be informed of all AE which are reported from other Investigators periodically.

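### Interim survival results by arm go to the steering committee as well as the independent DSMB, and the protocol does not say whose decision governs

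*Protocol*

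**What the plan says.** The interim text in section 5.1 of the Protocol gives the look an efficacy purpose: "With the interim analysis we will be able to evaluate whether there is a substantial superiority of one treatment". It then names who evaluates the results: "The obtained results will be evaluated by the DSMB and by the steering committee". It also attaches a trial-wide consequence: "in case of significant differences in survival among the groups, all patients will be switched to the most promising treatment". The same look is meant to check the assumptions behind the sample size.

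The opening paragraph of section 5.1 sets up an independent DSMB and describes its position as follows:

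- On data: "The DSMB will have access to all results".
- On stopping: "The DSMB has the right to stop the trial for safety reasons". No stopping right for efficacy is stated.
- On its rules: "The DSMB Charter will be prepared by the steering committee", to be signed by the DSMB members before the trial starts.

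The steering committee has operational duties elsewhere. It provides the eCRF (4.1), equips the centres together with the principal investigator (5.3) and supervises verification of source data (6.2). It also shares the rating of adverse events: "For every AE, the SC and the DSMB must assess the intensity (severity) and causality" (5.2). On masking, section 3.1 says: "The study is conceived as open-label".

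**The concern.** An independent monitoring board is normally the only body that sees outcomes by arm during a trial, so that those conducting it cannot be influenced by an early trend. Here the protocol sends the comparative results to the trial leadership by an explicit rule. It leaves open how the DSMB and the steering committee reach a decision together, and which view prevails if they differ.

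If the look leads to continuation, people who know mortality by arm would go on supporting the centres, co-rating adverse events and considering any change of sample size. An interim trend that became known at the centres could also alter co-intervention: section 2.3 places no restriction on concomitant treatment and leaves rescue treatment to clinical judgement. Rescue use is itself a secondary endpoint (2.4.2), and more rescue steroid use in the LMWH-alone group would dilute the contrast being tested.

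This is separate from the question of an interim significance boundary. Even with a boundary, the results would still reach the steering committee.

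**Working it through.** **Who sees what.** The interim rule turns on a survival difference among the groups. Whoever evaluates that needs deaths and denominators for each arm. The evaluators named are the DSMB and the steering committee. Access to by-arm mortality is therefore implied for both, although the protocol does not put it in those words. Nothing in the protocol text reviewed limits the steering committee to pooled data or to a recommendation.

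**Who decides.** The DSMB paragraph states a safety stop. The interim paragraph states a joint evaluation and a consequence, with no named decision-maker. Read together, they leave the efficacy decision shared and without a governing voice.

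**The plan's own sample size.** Inputs from section 2.6: mortality 50% against 25%, two-sided alpha 0.025, power 80%, allocation 1:1:1. With pooled variance under the null and no continuity correction:

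n per arm = [2.241 × √(2 × 0.375 × 0.625) + 0.842 × √(0.5 × 0.5 + 0.25 × 0.75)]² / 0.25² ≈ 70

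Three arms give 210, as stated, with power 80.0%.

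**Patients still to be randomised after the look.**

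- Upper bound, results available as soon as patient 90 is randomised: 210 − 90 = 120, and 120/210 = 57%.
- Look waits for 28-day outcomes. Section 2.7 gives 8 sites × 3 eligible patients = 24 per month, of whom 80% are enrolled: 24 × 0.80 = 19.2 per month. Over 28 days (about 0.92 month), 19.2 × 0.92 ≈ 18 more patients enter if recruitment does not pause. Then 120 − 18 = 102, and 102/210 = 49%.
- Time for data cleaning and analysis would lower this further; the protocol gives no figure for it.

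The interim text calls 90 patients half of the sample size, but 90/210 = 42.9%; 90 is half of 180. The figures above use 210, the total stated in 2.6 and 2.7.

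**How informative the released results would be.** At the look there are about 90/3 = 30 patients per arm.

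- Power for 50% against 25% at two-sided 0.025: Φ[(0.25 × √30 − 2.241 × 0.685) / 0.661] = Φ(−0.25) ≈ 40%.
- If mortality were 50% in every arm, simulation puts the chance that at least one steroid arm differs from LMWH alone by 10 points or more, in either direction, at about 74%.

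The steering committee would therefore often hold an apparent trend that says little about the true effect.

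**The case against.** Several points on the other side deserve weight.

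- **A reader might infer that the DSMB may stop only for safety and has no part in efficacy.** The text does not support that. Section 5.1 grants a safety stop without excluding others and gives the DSMB access to all results. The interim paragraph names the DSMB as one of the two bodies evaluating superiority. What is missing is a stated efficacy stopping right and a statement of who has the final say.
- **A reader might infer that the steering committee directs rescue treatment or attributes adverse events alone.** Section 2.3 leaves rescue to the attending physicians, and section 5.2 has the DSMB share the rating of adverse events. Whether committee members also treat or recruit patients cannot be checked, because the roles section was not in the text available. The co-intervention risk is therefore indirect: it needs knowledge of the trend to reach the centres.
- **The primary endpoint is robust.** All-cause death at day 28 needs little judgement to ascertain, and allocation is by central web-based randomisation with variable blocks. This stands, and it limits the concern.
- **The DSMB charter may set the order of review and the level of detail released.** It may, and it could narrow what the committee receives. It could not confine by-arm results to the DSMB without contradicting the protocol, which makes the committee an evaluator. The committee also prepares that charter.
- **The trial is open-label anyway.** Knowing one patient's allocation is different from knowing aggregate mortality by arm across 8 centres, so open-label treatment does not make the release harmless.

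**Conclusion.** The point holds as a matter of governance, and on explicit wording: interim survival results by arm are not confined to the independent DSMB, and the protocol does not say whose decision governs. The exposure is 57% of the planned patients at most, and about 49% if the look waits for day-28 outcomes. The second figure assumes the planned enrolment rate, no recruitment pause and no allowance for analysis time.

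The size of any bias cannot be derived from the document. A reader might go further and conclude that the primary mortality comparison is invalidated, or that the steering committee alone decides on efficacy. Neither follows: ascertainment of death is little exposed, and the evaluation is shared with the DSMB. This is an avoidable weakness that should be corrected before the look takes place.

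**What to change.** Amend section 5.1, including the interim paragraph, and write the DSMB charter to match:

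1. Interim results by arm are seen only by the DSMB and the statistician who reports to it.
2. The DSMB's remit includes recommendations on efficacy as well as safety.
3. The steering committee receives the DSMB's recommendation and pooled data only, and the text states who takes the final decision on that recommendation.

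The consequence that the interim paragraph attaches to a survival difference must be reconciled with this wording, so that it is clear on whose recommendation it would be triggered.

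The cost is a few sentences in the protocol and the corresponding charter text. The small downside is that the steering committee must act on a recommendation without seeing the by-arm data. The change works only if it is made before the interim results are released.

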### **2.6 SAMPLE SIZE**

The target sample size is based on the hypothesis that the combined use of UHF and steroids versus the LMWH group will significantly reduce the risk of 28-day death. The overall sample size in this study is expected to be 210 with a randomization 1:1:1. Assuming an alpha of 2.5% (two tailed) and mortality rate in LMWH group of 50%, as indicated from initial studies of ICU patients, the study will have an 80% power to detect at least a 25 % absolute reduction in the risk of death between:

a) LMHW + steroids group and LMWH group

or

b) UHF + steroids group and LMWH group

The study has not been sized to assess the difference between LMHW + steroids group and UHF + steroids group, therefore the results obtained from this comparison will need to be interpreted with caution and will need further adequately sized studies to be confirmed.

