## **4.2 STATISTICAL METHODS**

### **4.2.1 Methods for statistical analysis**

All patients enrolled in the study will be entered in the full analysis set independently of his/her treatment time. The intention to treat population will be considered for primary analysis. A descriptive statistical analysis will be performed to describe every relevant variable. In general, categorical data will be presented using counts and percentages, whilst continuous variables will be presented using the number of patients, mean, standard deviation, median, minimum, and maximum. Denominators for calculation of percentages will be taken as the number of non-missing responses in the specified analysis population and treatment group unless otherwise stated, and percentages will be rounded to one decimal. Minima and maxima will usually be reported to the same level of accuracy as the raw data; means, medians and standard deviations will be presented to one further decimal place; standard errors (if presented) will be presented to 2 decimal places more than the raw data. 97.5 % confidence interval will be calculated for primary outcome and for the relevant secondary ones. All data recorded in the CRF will be listed. Distribution of SAPSII and SOFA score (total and for single organ) at admission, P/F ratio distribution at baseline and at day 3, biomarkers PCR, PCT and IL-6 P/F ratio distribution at baseline and at day 3 will be summarized.

The comparison between

1. LMHW + steroids group and LMWH group
2. UHF + steroids group and LMWH group

with binary outcomes will be performed by using Relative Risks (RRs), whereas for continuous data, the difference of means (DMs) will be used. Comparisons involving time to event data will be displayed by using Kaplan-Maier survival curves and summarised by Hazard Ratios (HRs).

All measures of association will be presented with their confidence intervals. A result will be considered as statistically significant if its p-values will be less than 0.025 (2.5%).

The analyses will be performed by using STATA software.

As the study has not been sized to assess the difference between LMHW + steroids group and UHF + steroids group, the results obtained from this comparison will be reported and will be interpreted with caution. The main analyses will not take into account the factors of stratification.

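### The interim look ties a switch of all patients to a significant survival difference but sets no efficacy boundary; at the protocol's own 0.025, error per comparison is about 4.4%, not 2.5%

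*Protocol*

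**What the plan says.** Section 5.1, under the interim heading, places one look after 90 patients are randomised and calls this half of the sample size. Its purposes are safety, a check of the sample-size assumptions, and a judgement on whether one treatment is substantially superior. The consequence is stated: "in case of significant differences in survival among the groups, all patients will be switched to the most promising treatment". On who sees the data: "The obtained results will be evaluated by the DSMB and by the steering committee". The DSMB's own right to stop, stated earlier in section 5.1, is for safety.

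Section 4.2.1 calls a result significant when p is below 0.025. It names two comparisons, each steroid arm against LMWH alone. Section 2.6 uses the same level, two-tailed, for the sample size: "The overall sample size in this study is expected to be 210 with a randomization 1:1:1", and "the study will have an 80% power to detect at least a 25 % absolute reduction in the risk of death between" either steroid arm and LMWH. On the remaining pair it says: "The study has not been sized to assess the difference between LMHW + steroids group and UHF + steroids group".

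**The concern.** Switching every patient to one treatment ends the randomised comparison, so this is an efficacy decision and not only a safety review. It rests on the word significant, and the only meaning the protocol gives that word is p below 0.025. The final analysis then tests at the same 0.025. Two chances to declare success at an unreduced level cannot keep the error at 2.5% per comparison.

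The phrase about differences among the groups also covers the two steroid arms against each other. Read literally, the trial could stop on the one comparison that sections 2.6 and 4.2.1 say must be interpreted with caution.

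The primary mortality conclusion is at stake: it could come from about 30 patients per arm, with an exaggerated effect. If the trial continues, a steering committee that has seen results by arm remains in charge of an open-label study. Rescue steroids are given at clinicians' judgement (section 2.3), and the same committee assesses the causality of adverse events (section 5.2). That can bias later conduct.

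**Working it through.** **Inputs.** Alpha 0.025 two-sided, control mortality 50%, absolute reduction 25 points, power 80%, total 210 at 1:1:1 (section 2.6). Threshold 0.025 and two comparisons (section 4.2.1). Interim at 90 patients (section 5.1). Assumptions: 30 per arm at the interim and 70 at the end, with all day-28 outcomes known at each look.

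**1. The plan's own figure.** With pooled variance, mean risk 0.375 and no continuity correction:

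n = [2.2414·√(2·0.375·0.625) + 0.8416·√(0.5·0.5 + 0.25·0.75)]² / 0.25² = 69.97, so 70 per arm and 210 in total.

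The plan's figure is reproduced exactly, with the full 0.025 used at the final analysis.

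**2. Interim fraction.** 90/210 = 42.9%. A fraction of 50% would need a total of 180. Section 5.1 and section 2.6 disagree.

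**3. One comparison, two looks.** Under the null the interim and final statistics are bivariate normal with correlation √(30/70) = 0.655. With c = 2.2414 at both looks, P(|Z₁| > c or |Z₂| > c) = 4.4%, against 2.5% for one look. At a true 50% fraction it is 4.3%.

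**4. Family-wise error.** All three arms equal, shared control. A false positive is an interim trigger or a rejection of either planned comparison at the final 0.025. Normal theory uses 2 million runs at 90/210; the binomial check uses 1 million trials at 50% mortality.

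| Interim rule | Normal theory | Binomial |
|---|---|---|
| No interim look | 4.6% | 4.2% |
| One global three-group test at 0.025 | 6.4% | – |
| One global three-group test at 0.05 | 8.5% | – |
| Two planned comparisons at 0.025 | 8.0% | 8.0% |
| Any of three pairs at 0.025 | 9.7% | 9.8% |
| Two planned comparisons at 0.05 | 11.8% | 11.8% |
| Any of three pairs at 0.05 | 14.8% | 14.9% |

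At a fraction of 50% the normal-theory figures with an interim look are 0.2 to 0.3 points lower.

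**5. What triggers the switch.** In the binomial null at 30 per arm, some pair falls below 0.025 in 7.0% of trials. In 1.9% of trials the only such pair is the two steroid arms.

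**6. Size of effect at the trigger.** With 15/30 control deaths, 7/30 gives p = 0.032 and 6/30 gives p = 0.015 (uncorrected chi-square). The switch therefore needs an observed difference of 30 points. By Fisher's exact test 6/30 gives 0.029, so 5/30 (33 points, p = 0.013) is needed. Both exceed the 25-point design effect. If the true difference is 15 points (50% v 35%), about 15% of trials cross by the uncorrected test, and those show about 35 points on average.

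**7. With a strict boundary (each comparison held at 2.5%).**

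- Haybittle-Peto, interim p < 0.001: the final level is 0.0245 at 90/210. Leaving the final level at 0.025 gives 2.55% per comparison and 4.7% family-wise.
- O'Brien-Fleming-type spending: 0.0003 then 0.0249 at 90/210; 0.0008 then 0.0247 at 50%.
- Fixed-sample power with 70 per arm is 79.97% at 0.0249 and 79.8% at 0.0245.

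**The case against.** The strongest reply is that stopping boundaries are often put in a DSMB charter or SAP. Section 5.1 promises a charter, signed before the trial starts, and the SAP is not at hand. The 0.025 stands in the general analysis section and is not tied to the interim look, and the reference to substantial superiority may hint at a stricter standard. This stands in part: a reader might infer that no boundary exists anywhere, and the protocol cannot show that. But the protocol does more than stay silent. It fixes the action, fixes one significance level, and refers to no efficacy boundary in another document. Followed as written, it gives the errors above.

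A reader might also infer that the false-positive rate is simply double an intended 5%. The protocol does not support that. It states no overall 5%; the figure is inferred from 2 × 0.025. Near-doubling (9.7–9.8%) needs any pair at 0.025 to be able to trigger the switch. For the two planned comparisons the error is 8.0%, or 1.6 times 5%. The wording could also mean one global test, at 6.4%.

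Finally, a reader might blame the final test for keeping 0.025. Step 7 shows that this does almost no harm once the interim boundary is strict.

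**Conclusion.** The point holds: the rule is wrong as written because a decision that ends the comparison has no efficacy boundary. If the interim uses the protocol's own 0.025, the stated 2.5% per comparison becomes about 4.4%. That result needs no assumption about an overall target. Family-wise error rises from 4.2–4.6% to about 8% for the planned comparisons, or nearly 10% if any pair counts. Across readings it runs from about 6% to 15%, so no single multiple should be quoted without naming the reading.

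These figures assume equal arms under the null, complete day-28 outcomes at each look, and a final analysis of the two planned comparisons at 0.025. The mismatch between 90 patients and 50% barely changes them, but it does change the O'Brien-Fleming-type boundary. The protocol should be corrected before interim results by arm are seen, because a switch of all patients cannot be undone.

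**What to change.** In section 5.1 and the DSMB charter:

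- State a strict interim efficacy boundary for each of the two comparisons with LMWH. Examples are Haybittle-Peto at p < 0.001 with about 0.0245 at the end, or O'Brien-Fleming-type spending at 90/210 of about 0.0003 then 0.0249 (about 0.0008 then 0.0247 if the look is truly at 50%). Put the matching final level in section 4.2.1.
- Reconcile the 90 patients and the 50% with the total of 210.
- State that UFH + steroids against LMWH + steroids cannot support an efficacy conclusion at the interim.
- Give comparative interim results to the DSMB only; the steering committee receives a recommendation.
- Base the primary as-randomised comparison on data cut before any switch.

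The cost is a paragraph in each document. Early stopping for efficacy becomes less likely and the final level falls very slightly. Power stays about 80% and no extra patients are needed. These changes concern the statistical conclusion only; no rule on patients' treatment is proposed.

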## **2.4 OUTCOMES**

### **2.4.1 Primary Endpoint:**

- All-cause mortality at day 28.

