### **2.7 RECRUITMENT**

All centres participating in this study are experienced in investigator-initiated studies. On the basis of a conservative estimation, that 8 participating sites admit an average of 3 eligible patients per month per centre (24 patients/month). Assuming that 80 % of eligible patients are enrolled, recruitment of 210 participants will be completed in around 10 months. Every month, recruitment status will be evaluated, and a newsletter will be disseminated, including any practical, clinical or scientific issue arisen.

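### The interim look is triggered by randomisation with no day-28 follow-up condition, and its switch rule can change treatment inside the 28-day endpoint window without saying how those patients count

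*Protocol*

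**What the plan says.** The primary endpoint (Protocol 2.4.1) is "All-cause mortality at day 28".

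Under Analyses ad interim (Protocol 5.1), "an interim analysis is planned after the randomization of 90 patients". The stated purposes are safety, checking the event rate assumed for the sample size, and judging whether one treatment is substantially superior. No minimum follow-up, data cut-off or pause in recruitment is given. On a positive result the rule is that "in case of significant differences in survival among the groups, all patients will be switched to the most promising treatment". This is not limited to new patients or to patients past day 28.

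Protocol 4.2.1 enters every enrolled patient in the full analysis set whatever the treatment time. It makes intention to treat primary, compares binary outcomes by relative risk, and takes percentages over non-missing responses. It does not say how patients who are switched, or who are enrolled after a switch, are analysed.

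**The concern.** Two separate problems follow from these rules.

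**Maturity.** A count of randomised patients is not a count of known day-28 outcomes. If data are cut when the count is reached, the most recent recruits have no endpoint. The comparison that decides the switch then rests on fewer patients, and the event-rate check depends on how the unfinished patients are handled.

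**Crossover.** Patients who change treatment before day 28 have an endpoint that mixes two treatments but is credited to the original arm. If the chosen treatment is truly better, this narrows the contrast between arms. Patients enrolled after the switch all receive one treatment, so they have no concurrent randomised control, yet section 4.2.1 places them in the full analysis set.

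Waiting for day-28 data cures the first problem but not the second.

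**Working it through.** **Inputs**
- Section 2.6: "Assuming an alpha of 2.5% (two tailed) and mortality rate in LMWH group of 50"%; "the study will have an 80% power to detect at least a 25 % absolute reduction in the risk of death between" each steroid arm and LMWH; "The overall sample size in this study is expected to be 210 with a randomization 1:1:1".
- Section 2.7: "8 participating sites admit an average of 3 eligible patients per month per centre (24 patients/month"), of whom 80% are enrolled.
- Section 5.1: trigger at 90 randomised.
- Assumptions: uniform accrual and a month of 30.4375 days.

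**The plan's own figure.** Two proportions, pooled variance, no continuity correction, two-sided 2.5%, 80% power:

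n = [2.2414 × √(2 × 0.375 × 0.625) + 0.8416 × √(0.25 + 0.1875)]² / 0.25² = 69.97

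This gives 70 per arm and 210 in all. Power at 70 per arm is 80.0%, so the sample size reproduces.

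**Patients without day-28 status at the trigger**
- Accrual: 24 × 0.80 = 19.2 per month; 19.2 / 30.4375 = 0.631 per day.
- Inside 28 days: 0.631 × 28 = 17.7, about 18 of 90 (20%).
- Complete: 90 − 17.7 = 72.3, about 24 per arm.

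| Accrual | Inside 28 days | Share of 90 |
|---|---|---|
| half the plan | 8.8 | 10% |
| as planned | 17.7 | 20% |
| double the plan | 35.3 | 39% |

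**Power at the look, 50% versus 25%, p<0.025.** Section 4.2.1 states only this threshold, so it is used here. Power = Φ[(0.25√n − 2.2414 × 0.6847) / 0.6614].
- 30 per arm: Φ(−0.25) = 40%.
- 24 per arm: Φ(−0.47) = 32%.

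**Event-rate check.** Take a true 50% and assume deaths spread evenly over 28 days, so an unfinished patient has on average a 25% chance of having died by the cut. Expected deaths are 72.3 × 0.50 + 17.7 × 0.25 = 36.2 + 4.4 = 40.6. The same ratios hold within the LMWH arm, with every count divided by three.

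| Denominator | Calculation | Rate |
|---|---|---|
| all 90 | 40.6 / 90 | about 45% |
| known outcomes only, early deaths counted | 40.6 / (72.3 + 4.4) | about 53% |
| only patients with 28 days elapsed | 36.2 / 72.3 | 50% |

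**Patients in the window on a switch date.** Under steady accrual, entries and exits balance, so the number stays at 0.631 × 28, about 18, whenever the switch occurs:

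| Days after 90th randomisation | Randomised | Inside window |
|---|---|---|
| 0 | 90 | about 18 |
| 28 | about 108 | about 18 |
| 42 | about 116 | about 18 |

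With 1:1:1 allocation, two thirds are outside the chosen arm: 17.7 × 2/3 = 11.8, at most about 12. That is 11.8/60 = 20% of the patients in the other two arms at 90 randomised, or 11.8/71.8 = 16% at about 108. Both are upper bounds, because some will have died or finished study treatment.

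**The case against.** **The trigger fixes a count, not a data cut.** A look after 90 randomisations can still wait for day 28, and a DSMB charter or SAP, neither of which is shown, could say so. This stands. A reader might infer that the interim necessarily reads immature mortality. The text does not say that, and the 18 of 90 applies only if data are cut at the trigger. But the protocol sets the trigger itself, and a later cut leaves the crossover untouched.

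**The event rate need not be understated.** A reader might infer a downward bias from the 45%. That needs all 90 in the denominator, which no section prescribes. The non-missing denominator in section 4.2.1 could give about 53%, and Kaplan-Meier, which that section uses for time-to-event data, would stay near 50% under the same assumptions. What stands is that the direction is undetermined.

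**Crossover is limited.** A reader might infer that every patient under follow-up is affected, or that each month of review adds about 19 more. Neither holds. About a third are already in the chosen arm. Some others will have died: with deaths spread evenly and the planned rates, about 9 to 10 of the 12 would be alive. Some will be off study treatment, since study heparin ends at ICU discharge and the longest methylprednisolone course in section 2.3 ends at day 14. New entrants replace patients who reach day 28, so the number in the window does not grow.

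**The switch is conditional.** It needs a significant survival difference, and power at the look is only 32% to 40% under the design effect. True, but it is the only action the protocol states for a positive result, and that is when the primary estimate matters most.

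**Conclusion.** The point holds in two parts and should be corrected.

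1. The interim has no day-28 condition although it judges a day-28 endpoint. Cut at the trigger and at planned accrual, about 18 of 90 (about 9 to 35 for half to double accrual) are unfinished. Power falls from about 40% to about 32%, and the event-rate check can read about 45% or about 53% against a true 50%.
2. The crossover is the stronger part, because it remains however long the look is delayed unless recruitment pauses. About 18 patients are in the window on any switch date. At most about 12 of them would change treatment and count under their original arm, and later enrolees would enter the full analysis set without a concurrent control.

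These sizes rest on the planned accrual being met evenly, equal allocation and, for the event rates, deaths spread evenly over 28 days. The dilution of the treatment effect cannot be sized, because it depends on when in the window each patient changes. The documents do not support a claim that the look must be immature, that the event rate is biased downwards, or that all patients in follow-up are affected.

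**What to change.** In Protocol 5.1 (Analyses ad interim), with matching text in 4.2.1 and the DSMB charter:

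1. **Interim cohort.** Hold the efficacy look when the first N randomised patients, in order of randomisation, have all passed 28 days since randomisation. Use only that cohort for the survival comparison and the event-rate check. Do not define it as patients who have completed day 28 or died, because that admits early deaths among recent recruits and leaves out their living contemporaries (the 53% reading above).
2. **Analysis if a switch occurs.** The main randomised comparison uses patients randomised at least 28 days before the switch date, a cohort set by date and not by outcome. As a sensitivity analysis, report all patients randomised before the switch, as allocated, on day-28 status. Report patients enrolled after the switch separately as non-randomised. Censoring at the switch is not advised for the main analysis, since it does not fit a binary day-28 outcome compared by relative risk.
3. **Scope of the switch.** The sponsor and DSMB should state to whom it applies. That is a clinical decision and none is proposed here.

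The sponsor must settle N: 90 is labelled half the sample size, but 90/210 = 43%. That is a separate point.

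Cost: about one paragraph of text. The efficacy look comes about one month later, with about 108 randomised by then if recruitment continues, while DSMB safety monitoring carries on. If a switch occurs, about 18 patients leave the main comparison.
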